#### Mini-Mental State Examination

Mini-Mental State Examination was designed as a clinical method for grading cognitive impairment. The score ranges from 0 to 30: scores ≥ 24 indicate normality between 18 and 23 indicate mild cognitive impairment, between 11 and 17 average cognitive deficits, scores ≤ 10 severe cognitive impairments. The reported score is corrected according to age and education (35).

#### Functional Ambulation Categories

The scale is used to classify the severity level of gait disturbances in neurological disorders. It provides a hierarchical classification from level 0 (impossible walking) to level 5 (no limitation) (36).

#### Rankin Scale

It is a simple scale for the evaluation of the outcomes following a stroke. Reliability is well-defined. The individual categories are essentially based on patient mobility. There are 6 grades of classification from 0 to 5, where 0 means independence and 5 means severe disability (37).

#### Hoehn and Yahr Scale

This scale is used in the medical field to describe the symptoms of PD progression. It was originally published in 1967 in the Neurology Journal by Melvin Yahr and Margaret Hoehn, and included stages 1–5. Since then, a modified scale has been proposed, with the addition of stages 1.5 and 2.5 describing the intermediate course of the disease (38).

#### Geriatric Depression Scale 5-Items Version

This questionnaire assesses the current condition of the patient's mood. For the screening required by our study, only the first five items of the scale can be used. The answers highlighted indicate the statements expected by a non-depressed subject (39).

#### Barthel Index

Barthel index is an ordinal scale used to measure a subject's performance in everyday life activities. The index analyzes ten variables that describe the activities of daily life and mobility. A high overall score is associated with a greater probability of being able to live at home independently after discharge from the hospital (40).

#### SF-12 Health Survey

The SF-12 is composed of 12 items that produce two measurements related to two different aspects of health: physical health and mental health. The subject is asked to answer on how he feels and how he is able to carry out the usual activities, evaluating the current day and the four previous weeks (41).

#### Assistive Device Predisposition Assessment

The purpose of the tool is to assess the user expectations about technological devices (42).

#### Unified Theory of Acceptance and Use of Technology

The UTAUT (28) scale is made up of four constructs (performance expectancy, PE; effort expectancy, EE; social influence, SI; facilitating conditions, FC) that determine the level of acceptance of a technology by users, in terms of both attitudes toward the system (behavioral intention, BI) and its use (use behavior, USE). In addition, UTAUT incorporates four moderators (gender, age, experience, and voluntariness) that regulate the existing relationships between independent quantities (constructs) (PE, EE, SI, and FC) and dependent quantities (constructs) (BI, USE).

#### Tinetti's Scale or Performance-Oriented Mobility Assessment

Tinetti's scale is a tool used to evaluate balance and gait performance. The test is clinically used to determine the mobility status of a subject or to assess changes in balance and gait time. The total POMA (POMA-T) consists of two sub-scales: the balance evaluation scale (“balance scale” or POMA-B) and the gait evaluation scale (“gait scale” or POMA-G) (43).

#### Short Falls Efficacy Scale – International

The scale measures the “fear of falling.” The cut-offs for the fear of falling are divided as follows: a score between 7 and 8 indicates a low concern, between 9 and 12 a moderate concern, and between 14 and 28 a high concern (44).

#### Short Physical Performance Battery

The SPPB scale is a short battery of tests designed to assess the function of the lower limbs. This scale consists of three different sections: balance assessment, evaluation of walking on four linear meters, evaluation of the ability to perform, for five consecutive times, the sit to stand from a chair, without using the upper limbs. The total scale score, therefore, has a range from 0 to 12 (45).

#### Unified Parkinson's Disease Rating Scale – III

The UPDRS is the most widely used rating scale in assessing the prognosis of Parkinson's disease. The total number of items investigated in this clinical assessment is 65, which can be scored from 0 to 4. A score of 0 is given in a situation of normality with respect to the problem being investigated, while if there is a minimal impairment, 1 point is given, if it is mild it is indicated by 2 points, while if it is moderate it is marked with a 3, in a more serious situation a score of 4 is given (46).

#### Timed Up and GO

TUG is a simple test to measure a person's level of mobility and requires static and dynamic balancing skills. It measures the time and takes a person to get up from a chair, walk three meters, turn around, return to the chair and sit down again (47).

#### Six Minute Walking Test

6MWT is a test that allows measurement of a patient's residual functional capacity. The test is performed by asking the patient to walk for 6 min along a corridor with a rigid walking surface. The 6MWT is based on a so-called self-pace mode, i.e., the patient chooses the intensity of effort (48).

#### Goal Attainment Scale

GAS is a measure referring to an individualized criterion for assessing the achievement of objectives. Five possible levels are defined for each objective: −2 result much lower than expected; −1 result lower than expected; 0 achievement; +1 result higher than expected; +2 result much higher than expected. Behavioral objectives are usually measured dichotomously: as YES or NO, “achieved” or “not achieved” (49).

*Ad hoc scale on satisfaction with the SI-ROBOTICS intervention:* The scale consists of 47 items, the domains of which are:

Social Presence: its sub-dimensions are overall perceived social presence, psycho-behavioral interaction, and trust. The overall perceived social presence consists of six items. Subjects are asked to rate their opinion on a five-point scale. The psycho-behavioral interaction scale consists of five items. The trust scale consists of four items.HRI: its sub-dimensions are Language, Communication, and Perceived safety during movement. The language scale is composed of two items, built *ad-hoc* to verify the speech capability of the robotic platform. Communication is composed of three *ad-hoc* developed questions. Finally, the perceived safety scale is built on four items. Two of them are built *ad-hoc* for the project, while the other two are an adapted version of the standardized Godspeed tool on perceived safety, where users are asked to rate their emotional state in relation to the speed of the robot.Usability: its sub-dimensions are perceived as easy to use (four items), perceived usefulness (six items), and satisfaction with use (three items). All questions were constructed *ad-hoc* for the SI-ROBOTICS system.Acceptability: its sub-dimensions are anxiety (three items), attitude (three items), perceived adaptability (four items), and intention to use (four items). All questions were constructed *ad-hoc* for the SI-ROBOTICS system.

#### Instrumental Gait Analysis

Gait analysis will be performed through the G-Walk (BTS Bioengineering) during the 6MWT. G-Sensor is a wearable system for gait and movement assessment. It allows having a kinematic evaluation of the trunk and of the spatio-temporal parameters recorded during the different tests and integrated protocols.

### Risk Management and Mitigation

The risk of falling is major during any rehabilitation program. The SI-ROBOTICS platform is not only designed to partner dance with patients with PD, but also to motivate them during the training and to capture information on kinematics at a secure distance. Moreover, the robotic platform is equipped with obstacles avoidance sensors at the basis to counteract the risk of hurting the participants during the performance. However, a dedicated physiotherapist will be present and will supervise the entire session, in order to intervene promptly in case of fall risk or any other emergency.

In case a fall occurs, the physiotherapist will follow this procedure: they will ask the patient to stay still before checking for pain, loss of sensation (feeling), and loss of movement in arms and/or legs which might indicate a fracture. If there is no evident injury and no signs of a change in health, in line with the person's wishes they allow them to get up independently if possible, or assist the patient in doing so. However, any adverse event related to the training will be covered by the Institution's insurance.

### Data Management

The project committed to the maintenance of participants' anonymity and confidentiality throughout all procedures, such as screening, recruitment, testing, evaluation, and dissemination procedures. Data collection, usage, and storage procedures complied with national laws and the EU's General Data Protection Regulation (GDPR) such as the commitment of participants' the right to access, right to be informed, right to withdraw, and right to data erasure. Data collection will be compliant with the principle of data minimization, i.e., the collection of personal information from study participants will be limited to what is directly relevant and necessary to accomplish the specific goals of the testing and evaluation work packages. Data entry will be carried out using specific software, providing blocks, and data entry checks, in order to reduce the number of entry errors. All screening data were will be discarded upon the project completion. During the testing procedures, all visual, auditory, and sensory data that the robot collects and processes in order to function as planned will be discarded after the procedures have been completed. The exception to this is the collection of the number of interactions that the robot logs with each participant. However, these interactions will be anonymous. All research data shall be made openly available for secondary analysis 3 years after the project completion.

### Data Analysis

The first step of the data analysis will deal with the description of the sample. Continuous variables will be reported as either mean and standard deviation or median and interquartile range on the basis of their distribution (assessed using the Kolmogorov–Smirnov test). Categorical variables will be expressed as an absolute number and percentage. The Mann–Whitney *U*-tests (for non-normal distribution), or the chi-square tests (normal or non-normal) will be used to compare the independent and dependent variables between the pre- and post-conditions, in addition to simple descriptive statistics (means, medians, and SDs as appropriate).

In order to verify the achievement of the primary endpoint (i.e., acceptability of the SI-ROBOTICS system), subscales of the UTAUT will be calculated. Means and standard deviation or medians and IQR of the scores will be reported according to their distribution. Correlation coefficients (Pearson for normally distributed variables, Spearman for non-normally distributed variables) of the UTAUT sub-scales with the other rating scales at each stage of the study and with the main characteristics of the subjects will be calculated to check for potential determinants of higher acceptability.

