## Methods and Analysis

### Trial Design

The study is designed as a technical feasibility pilot to test the SI-ROBOTICS system on a group of 20 older people with PD at an early stage (Hoen and Yahr Scale 1–2), during an Irish set dancing training. Assessment will be performed at the baseline (T0), after 4 weeks (mid-T1), and after 8 weeks of intervention (end-T2).

The primary aim is to evaluate the acceptability of the SI-ROBOTICS system in a group of patients with PD while performing a rehabilitation treatment based on Irish dancing, using the Unified Theory of Acceptance and Use of Technology (UTAUT) scale (28).

The secondary aim is the analysis of the modification of dimensions related to the general functional status, in terms of gait, balance, fear of falling, cardio-respiratory performance, motor symptoms related to PD, and quality of life.

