### Intervention

For this study, 20 patients with PD will be enrolled. Sixteen therapy sessions of 50 min will be conducted (two training sessions per week, for 8 weeks), involving two patients at a time. Cardiac and respiratory activity monitoring will be conducted during dancing treatments in order to detect heart rate and breathing frequency. Participants will have to complete at least 80% of the sessions.

Each session will involve the following activities:

breathing, relaxation, and postural harmonization exercises (5 min);active mobility and stretching exercises (5 min);Irish dancing with the SI-ROBOTICS system (35 min);relaxation exercises (5 min).

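### Pre/post comparisons of the secondary outcomes in a single group of 20 patients are assigned to independent-sample tests, and normally distributed continuous outcomes are left with chi-square only

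*Protocol article*

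**What the plan says.** The Trial Design section describes a "technical feasibility pilot to test the SI-ROBOTICS system on a group of 20 older people with PD at an early stage" and no comparator. The same patients are measured repeatedly: "Assessment will be performed at the baseline (T0), after 4 weeks (mid-T1), and after 8 weeks of intervention (end-T2". Table 2 schedules SF-12, POMA, FES-I, SPPB, UPDRS-III, TUG, the 6-minute walk and GAS at both T0 and T2. UTAUT, the primary measure, appears at T2 only.

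The Data Analysis section names two tests. Mann–Whitney U is reserved for non-normal distributions. The alternative reads "or the chi-square tests (normal or non-normal) will be used to compare the independent and dependent variables between the pre- and post-conditions". No paired t-test, signed-rank test, McNemar test or repeated-measures model is named anywhere in the article. The section does expect some variables to be normal: it plans means and SDs where the distribution allows, and it chooses its correlation coefficients by the rule "Pearson for normally distributed variables, Spearman for non-normally distributed variables".

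The primary endpoint is handled separately, by descriptive UTAUT subscale scores and their correlations with other scales and patient characteristics.

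**The concern.** There are two faults in one sentence.

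- **Wrong dependence structure.** Mann–Whitney U and the ordinary chi-square test compare two independent samples. Here the pre and post values come from the same patients. If the two values correlate positively, an independent-sample test overstates the variance of the change. Its true type I error then falls below nominal, and it misses real changes.
- **No test for normal continuous outcomes.** With Mann–Whitney confined to non-normal data, chi-square is the only test left for a normal variable. It is a test for categorical data, and its use does not depend on whether a distribution is normal.

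The secondary aim is to study change in functional status, gait, balance, fear of falling, motor symptoms and quality of life. These pre/post tests are the only tests of change that the article states. The Discussion plans a larger study, and a false finding of no change here could misinform it.

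**Working it through.** **Inputs from the article.** One group (Trial Design); n = 20 ("For this study, 20 patients with PD will be enrolled", Intervention); the tests listed in Data Analysis. It gives no power, alpha, SD, effect size or sample-size formula, so there is no stated figure to reproduce.

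**Assumptions.** Two-sided alpha 0.05; all 20 pairs complete; bivariate normal data with equal SDs; pre/post correlation ρ from 0 to 0.9; true change 0, 0.3, 0.5 or 0.8 SD.

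**Why pairing matters.** The variance of the mean change is 2σ²(1−ρ)/n. An independent-sample test in effect uses 2σ²/n. The correct standard error is therefore √(1−ρ) times the one used: 0.71 at ρ = 0.5 and 0.55 at ρ = 0.7.

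**Simulated rejection rates, Mann–Whitney / Wilcoxon signed-rank** (10,000 replicates; 3,000 for signed-rank):

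| ρ | No change | 0.3 SD | 0.5 SD | 0.8 SD |
|---|---|---|---|---|
| 0 | 5.0% / 4.8% | 14.7% / 13.7% | 32.1% / 29.5% | 66.8% / 65.2% |
| 0.3 | 2.5% / 4.8% | 11.2% / 18.2% | 29.0% / 41.7% | 69.3% / 80.9% |
| 0.5 | 0.8% / 4.9% | 8.0% / 23.7% | 27.5% / 55.2% | 72.4% / 91.1% |
| 0.7 | 0.1% / 4.9% | 4.6% / 35.4% | 24.1% / 76.3% | 77.8% / 99.2% |
| 0.8 | 0.0% / 4.5% | 3.0% / 49.6% | 21.2% / 90.5% | 81.8% / 100% |
| 0.9 | 0.0% / 5.1% | 1.3% / 78.7% | 18.7% / 99.6% | 87.4% / 100% |

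The paired t-test differs from the signed-rank test by at most about 2.5 percentage points. Repeat runs put the pair at ρ = 0.5 and 0.5 SD at 27–28% against 53–55%. That spread is about what Monte Carlo error allows: with 3,000 replicates the standard error is √(0.55 × 0.45 / 3000) ≈ 0.9 percentage points.

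**Cross-check of the paired column.** Approximate power is Φ(d√n / √(2(1−ρ)) − 1.96).
- d = 0.5, ρ = 0.5: Φ(2.236/1 − 1.96) = Φ(0.276) ≈ 61%.
- d = 0.5, ρ = 0.7: Φ(2.236/0.775 − 1.96) = Φ(0.927) ≈ 82%.

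These sit slightly above the simulated paired t-test (57% and 78%), as a normal approximation should at n = 20.

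**Share of power lost, 1 − (Mann–Whitney / signed-rank).**
- 0.5 SD: ρ = 0.3, 1 − 0.290/0.417 = 30%; ρ = 0.5, 1 − 0.275/0.552 = 50%; ρ = 0.7, 1 − 0.241/0.763 = 68%.
- 0.8 SD: ρ = 0.3, 1 − 0.693/0.809 = 14%; ρ = 0.5, 1 − 0.724/0.911 = 21%; ρ = 0.7, 1 − 0.778/0.992 = 22%.

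**Binary illustration (invented data).** Suppose 8 of 20 patients meet a criterion before and 14 of 20 after, with 6 improving and none worsening. Chi-square gives p = 0.057 (0.112 with continuity correction). McNemar's exact test gives 2 × 0.5⁶ = 0.031.

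**The case against.** The fairest defence has four parts.

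- **Small reach.** This is a feasibility pilot whose primary endpoint is untouched. Descriptive statistics accompany the tests. With positive correlation the error is conservative, so it hides change and does not create it. All of this stands and limits the consequence, but the test named is still the wrong one.
- **Size depends on assumptions.** This also stands. A reader might infer that the plan always throws away most of its power. The documents give no correlation or effect size to support that: the loss is nil at correlation 0 and modest for large changes.
- **Many scales are bounded scores.** POMA, SPPB and FES-I may well fall in the non-normal branch, so the chi-square gap mainly concerns measures such as gait speed and TUG. This narrows the second fault but does not remove it.
- **Detail belongs in a fuller plan.** This does not stand. The article chose to name the tests, and a fuller document could only repeat the error or contradict it.

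Three further inferences should be resisted. The T1 data are not unused, because Data Analysis correlates UTAUT with the other scales at every stage. Training "involving two patients at a time" does not establish a neglected clustering problem, because the article does not say that pairs are fixed. Nor is every inference on the secondary outcomes affected, because the correlations do not use these tests.

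**Conclusion.** The sentence is wrong as written. It prescribes independent-sample tests for same-patient comparisons and leaves normally distributed continuous outcomes without a test of means. That conclusion rests on the text alone.

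The size rests on the assumed values (n = 20 complete pairs, two-sided 5%, normal data). Mann–Whitney's type I error falls to about 1% at correlation 0.5 and to 0.2% or less at 0.7 and above. At a 0.5 SD change, about half the power goes at correlation 0.5 and about two thirds at 0.7. The fault is confined to pre/post tests of the secondary outcomes. It should be corrected before analysis because the error is plain and the correction nearly free.

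**What to change.** Replace the sentence on pre/post tests with:

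> Change from T0 to T2 will be tested with the paired t-test (approximately normal differences) or the Wilcoxon signed-rank test (otherwise, including ordinal scores). Paired binary variables will use McNemar's exact test. Mean or median change will be reported with a 95% confidence interval and described as uncontrolled change.

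Normality should be judged on the within-patient differences, not on the T0 and T2 values separately. A mixed model or Friedman test that also uses T1 is optional. If one is added, the text should say which analysis governs, so that no outcome has two competing tests.

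The cost is a few sentences of analysis text, with no new patients, visits or data.

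### Pre/post change in one group of 20 patients is to be tested with independent-samples tests, which ignores the pairing and makes the secondary comparisons over-conservative

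*Protocol article*

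**What the plan says.** Under Trial Design the study is a technical feasibility pilot "to test the SI-ROBOTICS system on a group of 20 older people with PD at an early stage". The Intervention section repeats the number: "For this study, 20 patients with PD will be enrolled". No comparison group is described anywhere. On timing: "Assessment will be performed at the baseline (T0), after 4 weeks (mid-T1), and after 8 weeks of intervention (end-T2". Table 2 lists POMA, short FES-I, SPPB, UPDRS-III, TUG and the 6-minute walk at all three visits, and SF-12 and GAS at T0 and T2.

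The pre/post comparisons serve the second aim: "The secondary aim is the analysis of the modification of dimensions related to the general functional status".

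The Data Analysis section names two tests for them: "The Mann–Whitney *U*-tests (for non-normal distribution") and, as the alternative, chi-square tests, whether the data are normal or not. These tests "will be used to compare the independent and dependent variables between the pre- and post-conditions". Descriptive statistics are to be given as well. For the primary endpoint the plan is that "subscales of the UTAUT will be calculated" and summarised, with correlations against the other scales and patient characteristics. No paired or repeated-measures method appears in the article.

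**The concern.** The Mann–Whitney U test and the ordinary chi-square test both compare two independent sets of people. Here the before and after values come from the same people, so 20 pairs would be treated as 40 unrelated patients. All stable differences between patients then stay in the error term, although the design allows them to be removed. With no control group and only 20 patients, pairing is the main source of precision for the secondary aim.

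The same sentence has two further faults. It gives chi-square, a test for categories, to data that may be normal or non-normal, which leaves normally distributed continuous change without a usable test. It also applies the pre/post comparison to independent as well as dependent variables, although several variables in Table 2 (socio-demographics, Barthel Index, ATDPA) are recorded only at T0 and have no later value.

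At stake is whether real changes in gait, balance, function, motor symptoms or quality of life are recognised. A spurious finding of no change could follow from the choice of test alone.

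**Working it through.** **Inputs from the article.** One group, 20 patients, the same patients at T0, T1 and T2; Mann–Whitney U or chi-square for pre against post. The article states no power calculation, so there is no figure to reproduce.

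**Assumptions (not in the article).** Two-sided alpha 5%; change d = 0.3, 0.5 or 0.8 SD; pre/post correlation ρ from 0 to 0.9; normal scores with equal SDs; no dropout.

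**Step 1: standard error of the mean change.**
- Ignoring pairing: SD × √(2/20) = 0.316 SD.
- Respecting it: SD × √(2(1 − ρ)/20), which is 0.224, 0.173, 0.141 and 0.100 SD at ρ = 0.5, 0.7, 0.8 and 0.9.
- Ratio 1/√(1 − ρ): 1.4, 1.8, 2.2 and 3.2.

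**Step 2: benchmark if the 40 values really were independent.** Power = Φ(d/0.316 − 1.96), giving 16%, 35% and 72% for d = 0.3, 0.5 and 0.8. Simulated Mann–Whitney at ρ = 0 gives 16%, 33% and 67%, which agrees.

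**Step 3: simulation with paired data.** 4,000 runs per cell, 20 pairs; signed-rank uses the exact critical value of 52. Monte Carlo standard error is at most √(0.25/4000) = 0.8 points. Repeat runs gave figures within about 1 to 2 points.

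Actual type I error of Mann–Whitney at nominal 5%: 2.0% at ρ = 0.3, 0.8% at 0.5, 0.1% at 0.7, near 0 at 0.8 or more.

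Power, Mann–Whitney against signed-rank:

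| ρ | d = 0.3 | d = 0.5 | d = 0.8 |
|---|---|---|---|
| 0 | 16% / 15% | 33% / 31% | 67% / 65% |
| 0.3 | 10% / 17% | 29% / 42% | 70% / 79% |
| 0.5 | 7% / 23% | 27% / 54% | 72% / 92% |
| 0.7 | 4.5% / 36% | 25% / 77% | 78% / 99% |
| 0.8 | 3% / 52% | 21% / 90% | 81% / 100% |
| 0.9 | 1% / 79% | 19% / >99% | 88% / 100% |

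Share of signed-rank power lost = 1 − (Mann–Whitney power / signed-rank power), for ρ from 0.5 to 0.9: 68% to 99% at d = 0.3, 49% to 81% at d = 0.5, and 12% to 21% at d = 0.8. At ρ = 0 nothing is lost.

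**Step 4: binary items.** For 30% before and 60% after, with latent ρ = 0.5, 0.7 and 0.9, chi-square has about 44% power throughout, against 56%, 70% and 87% for the asymptotic McNemar test. The exact McNemar test gains much less: four changes all in one direction give an asymptotic statistic of 4 (above 3.84) but an exact p of 2 × 0.5⁴ = 0.125. A check of the same setting with 40,000 runs put exact McNemar at about 45%, 51% and 57%.

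**Step 5: the loss expressed as sample size.** For 80% power at d = 0.5, the unpaired normal formula needs 2 × ((1.960 + 0.842)/0.5)² = 62.8, so 63 per occasion. The paired formula multiplies 62.8 by (1 − ρ): 32, 19, 13 and 7 pairs at ρ = 0.5, 0.7, 0.8 and 0.9.

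**The case against.** The strongest reply is that little depends on these tests. The trial is a feasibility pilot whose primary aim is acceptability. UTAUT is measured only at T2 and is analysed by summaries and correlations, so no pre/post test touches it. The article ties no efficacy hypothesis or decision rule to the secondary p-values. Means or medians are reported alongside, so the visit values stay visible. With positive correlation the error is conservative and does not produce false claims of benefit. All of this stands. It limits the reach of the point but does not make the named tests right.

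A reader might infer that most of the power is always lost, or that real changes will mostly be reported as no change. The article does not support that, because it gives neither an effect size nor a correlation. The statement fits small to moderate changes with correlation above about 0.5; a change of 0.8 SD would usually still be detected.

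A reader might also infer that the larger study foreseen in the Discussion would be left without an SD of change. The Discussion does not say that this pilot will size that study, and the SD of change can be computed from linked data whichever test is used.

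The simulation uses continuous normal scores, whereas the plan reserves Mann–Whitney for non-normal data and several scales are bounded integers (SPPB 0 to 12, short FES-I up to 28). The percentages are therefore illustrative.

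Leaving detail to a fuller plan is no answer, because the article names specific tests that contradict its own design. Nor is linkage a barrier: correlating T2 UTAUT with scales from each stage already requires linked records.

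**Conclusion.** The analysis is wrong as written. Independent-samples tests are named for a within-patient comparison, and normally distributed continuous change has no suitable test. With any positive pre/post correlation, p-values for the secondary pre/post outcomes are too large.

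The direction is certain given positive correlation. The size depends on the assumed effect and correlation: severe for small to moderate changes in strongly correlated scores, modest for large changes, and nil at zero correlation. For binary items the power gain from an exact paired test is small, and the reason to change is mainly that the test should match the data. The consequence is confined to the secondary outcomes and is one of missed changes.

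**What to change.** Replace the sentence on Mann–Whitney and chi-square tests with a within-patient analysis:
- **Scores, T0 to T2:** Wilcoxon signed-rank test, or the paired t-test when the differences (not the separate visit values) are approximately normal.
- **Binary variables:** exact McNemar test.
- **Multi-category variables** (for example FES-I concern levels or GAS levels): a paired ordinal or marginal-homogeneity test, or signed-rank.
- **Where T1 is included:** a repeated-measures method, Friedman or a mixed model.
- **Reporting:** the change with its 95% confidence interval.
- **Scope:** only variables measured both before and after, so T0-only and T2-only items drop out of the pre/post testing.

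Cost: one or two sentences of analysis text. No new data, patients or visits.
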